#### *Post-surgical intervention*

After surgery, participants will be randomized again to either a post-surgical intervention or to treatment as usual. The post-surgical intervention is comprised of a web-based ACT intervention with the cognitive activation model of stress as theoretical vantage points. The intervention consists of videos in combination with a work booklet targeting three main processes derived from the ACT hexaflex model (57), and delivered in two stages. In the initial stage, the intervention has several videos that is built to involve the patient in a broadening of their perspective of what can constitute maintaining and debilitating factors when experiencing persistent pain and/or fatigue. These initial videos involve a biopsychosocial explanation of pain and fatigue, alongside an introduction to mindfulness, values-based living, and stress reduction through cognitive behavioral techniques.

The next stage of the intervention involves the use of a hand-out booklet that serves as an addition to numerous videos presented to the participants. The videos are sorted in three categories aimed to communicate the six processes in a commonsensical, patient friendly way. The three categories are referred to as the tri-flex in the Focused ACT model (58), and consists of Aware (present-moment awareness and self-as-context), Open (Accept and defusion) and Engaged (values and committed action).

Within the booklet there are written tasks corresponding to different videos and scenarios shown in the online intervention to approximate previous trials showing efficacy on chronic pain from a similar intervention (59).

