### **Drop out and non-compliance**

Participants who no longer wish to participate in the study can inform the research group of their decision by notifying the study nurse, the trial coordinator or the PI. The trial

coordinator will in any case contact participants who drop out by phone, and ask if they are willing to report the reason for withdrawal. If reasons are provided, these will be registered on a dedicated drop out form. Whether they only want to withdraw from the interventions, or if they also want to withdraw from future follow-ups, will also be registered. Finally, it will be registered if the participant gives permission for use of data that has already been collected, or if they want these to be deleted. Participants who drop out of the study will still be included in the intention-to-treat (ITT) analyses, unless they required all their data deleted.

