### ***Statistical analyses***

Effect analyses of primary and secondary outcomes will be performed according to both the intention-to-treat principle and per protocol. The effect analysis of the primary outcomes will

involve a comparison of pain and fatigue levels at 3 months follow-up. Additionally, they will be analyzed using linear mixed models (also referred to as multilevel models) at the 3 different time points (post-surgery, 3- and 6-months f/u). Multilevel modelling is a flexible statistical approach that can handle non-balanced data with missing entries and repeated observations (61). The health economic analyses will investigate differences in treatment costs, as well as indirect costs related to work (dis)ability and sick-leave. A cost-utility analysis will be performed estimating costs per quality-adjusted life year.

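### Women who leave follow-up before 3 months are promised a place in the ITT analyses but have no value in the stated primary comparison, and for fatigue none in the added mixed model either

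*Protocol*

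**What the plan says.** The protocol's Drop out and non-compliance section sets the analysis rule: "Participants who drop out of the study will still be included in the intention-to-treat (ITT) analyses, unless they required all their data deleted". It recognises two degrees of withdrawal: "Whether they only want to withdraw from the interventions, or if they also want to withdraw from future follow-ups, will also be registered". The trial coordinator telephones every drop-out and asks for the reason.

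The Statistical analyses section says the primary effect analysis will "involve a comparison of pain and fatigue levels at 3 months follow-up". It continues: "Additionally, they will be analyzed using linear mixed models (also referred to as multilevel models) at the 3 different time points", and lists these as post-surgery, 3 months and 6 months. Multilevel models, it says, "can handle non-balanced data with missing entries and repeated observations".

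Two other sections matter. Outcome Measures assigns NRS and VAS ratings to discharge, with VAS for fatigue, and names NRS and FACIT-F for pain and fatigue at 3 months. Data collection and management places questionnaires before surgery, a brief phone survey at discharge, and questionnaires at 3 and 6 months.

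**The concern.** The rule that keeps drop-outs in the ITT analyses covers women who leave follow-up but allow their earlier data to be used. The primary analysis is built on one occasion, so a woman with no 3-month score has nothing to put into it. The mixed model might be expected to cover this gap, but it is only an addition, it starts after surgery, and for fatigue the discharge scale is not the scale of the primary outcome.

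If the women who leave follow-up differ from those who stay, and leave at different rates by arm, the 3-month comparison carries that selection. The pre-surgery data are the one self-report collected before either intervention and before these losses begin. The stated method does not use them.

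**Working it through.** **1. Who supplies which score under the stated methods**

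| Woman | NRS, 3-month comparison | NRS, mixed model | FACIT-F, 3-month comparison | FACIT-F, mixed model |
|---|---|---|---|---|
| Stops interventions only, stays in follow-up | yes | yes | yes | yes |
| Leaves follow-up after the discharge call, before 3 months | no | discharge score only | no | none |
| Leaves follow-up before the discharge call | no | none | no | none |

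The first row follows from the two recorded degrees of withdrawal. The FACIT-F entries in the second row follow from Outcome Measures, which gives fatigue a VAS at discharge and FACIT-F at 3 months. A mixed model tolerates missing occasions, but it cannot use a woman who has no observation on the scale being modelled. With a pre-surgery score of the same scale as an occasion, the second and third rows would each supply at least one value for both outcomes.

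**2. The plan's sample size and its margin**

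Inputs from Sample size and power: NRS difference 1, SD 2.4, two-sided alpha 0.05, power 0.80, 100 recruited per group.

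- Normal approximation: n = 2 × (1.960 + 0.842)² × 2.4² / 1² = 90.4, rounded up to 91. The t-test version gives 91.4, rounded up to 92. The stated 92 reproduces.
- Margin for missing 3-month scores: 1 − 92/100 = 8% for pain and 1 − 87/100 = 13% for fatigue.
- No attrition rate is stated. Assume 20% drop out, and take the section's two groups of 100 at face value. Power for pain then depends on how many drop-outs stay in follow-up:
  - none stay: n = 80, power 0.745
  - half stay: n = 90, power 0.794
  - all stay: n = 100, power 0.834

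**3. Illustrative bias in the 3-month pain comparison**

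Let p be the proportion leaving follow-up in an arm and g the amount by which leavers' mean pain exceeds stayers', taken as equal in both arms. The stayers' mean understates the arm's mean by p × g. The bias in the contrast is therefore (p in iACT − p in TAU) × g, in favour of iACT when p is larger there and leavers are worse off.

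- Assumed 20% vs 8%, g = 1.5: 0.12 × 1.5 = 0.18 NRS points. That is 18% of the planned difference, or 0.18/2.4 = 0.075 SD.
- Assumed gap in p of 5 to 15 percentage points, g of 1 to 2: 0.05 × 1 = 0.05 up to 0.15 × 2 = 0.30.
- If half of the drop-outs in the first scenario stay in follow-up: (0.10 − 0.04) × 1.5 = 0.09.

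None of these rates or gaps is in the protocol. No figure is offered for FACIT-F, for which the protocol states no SD.

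**The case against.** A reader might infer that the withdrawal rule collects nothing from drop-outs at 3 months, so that the primary result is simply a completers' comparison. The protocol does not support this. It records withdrawal from the interventions separately from withdrawal from follow-up, and nothing stops the 3-month questionnaire for the first group. The Compliance section treats use of the videos and booklet as something to log, not as a condition for staying in follow-up. This also weakens the argument that iACT's workload will drive differential loss: women who tire of the material are the ones an intervention-only withdrawal serves.

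A second tempting inference concerns women who leave between the two randomisations. Since "After surgery, participants will be randomized again to either a post-surgical intervention or to treatment as usual", such a woman has no iACT or TAU allocation. The protocol does not say that she will be analysed in the hypotheses comparing full sequences, and she still belongs to the first-stage comparison. Drawing both allocations at enrolment would trade this for a diluted iACT contrast, so it is not recommended here.

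Four further objections stand in part:

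- Imputation and sensitivity analyses are commonly left to the SAP, which is not at hand, so their absence is not counted. The choice of occasions and of a 3-month-only primary comparison is fixed in the protocol itself.
- Drop-outs may still contribute to the prescription and sick-leave outcomes through registries. The point is therefore confined to the self-reported primary outcomes.
- The protocol does not list NRS or FACIT-F among the pre-surgery questionnaires, so the remedy depends on confirming that they are there.
- The withdrawal section says what is registered and does not forbid reduced follow-up. Offering it is an improvement, not the correction of an error.

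**Conclusion.** The point holds for one group: women who leave follow-up before 3 months without asking for their data to be deleted. They are promised inclusion in the ITT analyses, yet the primary comparison as written cannot include them. For FACIT-F the additional mixed model cannot include them either. For NRS pain it can, if they answered at discharge.

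The consequence is modest and cannot be sized from the protocol. The range of 0.05 to 0.30 NRS points assumes that leavers are worse off, that more of them are in iACT, and that every drop-out leaves follow-up; it shrinks if some stay. It is an illustration, not an estimate. The margin for lost 3-month pain scores is 8%. The change is worth making because it improves the stated method at almost no cost.

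**What to change.** In Statistical analyses, take the primary 3-month contrasts for NRS pain and FACIT-F from the mixed model, with the pre-surgery score of the same scale included as an occasion. First confirm that both scales are in the pre-surgery questionnaires, and add either one that is missing. Every randomised woman with any score then contributes to the comparisons for which she has an allocation, and the contrast is adjusted for baseline. A woman with only a pre-surgery score adds little information on her own, and the model does not remove bias from drop-out that depends on unobserved 3-month scores. That is why the second change is also needed.

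In Drop out and non-compliance, state that women who withdraw only from the interventions continue follow-up. At the call the coordinator already makes, offer women who decline the full questionnaires a reduced option: the single-item NRS and the 13-item FACIT-F at 3 months.

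The cost is protocol wording, one field on the drop-out form and a few short contacts. At the 8% margin this is at most 0.08 × 200 = 16 women; under the assumed 20% and 8% rates it is at most 20 + 8 = 28. No extra patients are needed, and randomisation stays as planned.

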## **Analyses**

### ***Sample size and power***

Sample size is estimated for both of the primary outcomes. Previous trials with similar interventions have demonstrated moderate/large effect sizes on pain and fatigue (26, 60). However, compared to these studies, we expect more heterogeneity in our data as our study population will undergo several medical treatments during the trial (e.g. radiotherapy or chemotherapy after surgery). We thus expect a minimum difference of one point on NRS (0-10) and 3 points on FACIT-F (which corresponds to patients reporting being “slightly better”). Based on previous studies, it is expected that the control group scores 5 (SD: 2.4) on NRS at 3 months follow-up (25), and 18 on FACIT-F (26). With power set at 0.80 and two-tailed  $\alpha$  set at .05, the number needed in each group to detect the change in pain is  $n=92$ , and in fatigue  $n=87$ . To account for attrition and loss to follow-up, we plan to include 100 patients in each group.

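### Pain and fatigue are each sized at two-sided .05 and 0.80 power with no success rule: an either-outcome claim carries about 8-10% family-wise error, a both-outcomes claim about 0.67-0.73 power

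*Protocol*

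**What the plan says.** Under Sample size and power the protocol states "Sample size is estimated for both of the primary outcomes". The targets are a "minimum difference of one point on NRS (0-10) and 3 points on FACIT-F", with the expectation that "the control group scores 5 (SD: 2.4) on NRS at 3 months follow-up". For FACIT-F only a control mean of 18 is given, with no SD. One power and one alpha then serve both calculations: "With power set at 0.80 and two-tailed" alpha "set at .05, the number needed in each group to detect the change in pain is" 92, and for fatigue 87. The plan is to include 100 per group.

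Under Statistical analyses, "Effect analyses of primary and secondary outcomes will be performed according to both the intention-to-treat principle and per protocol". The primary effect analysis will "involve a comparison of pain and fatigue levels at 3 months follow-up". Linear mixed models over three time points follow as an additional analysis.

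Hypothesis 3, under Aims and objectives, expects the combined intervention to give less pain and less fatigue, and fewer pain prescriptions, at 3 months. The protocol does not divide alpha, order the two tests, or say whether a positive trial needs one outcome or both.

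**The concern.** With two primary outcomes, the error rate and power of the trial's main claim depend on how the two results are combined. Testing each at .05 and claiming success on either gives two chances of a false positive. Requiring both controls the error, but the power of the claim is then the chance that both tests succeed, which is below the power of either alone. The protocol sizes each outcome as if it were the only one and leaves the combination open, so the trial could be read under whichever rule suits the results.

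The pairing of intention-to-treat and per-protocol analyses adds to this. If the two disagree on a primary outcome, the text does not say which one settles it.

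**Working it through.** **Inputs from the protocol (Sample size and power).** Pain difference 1, SD 2.4, so d1 = 1/2.4 = 0.417. Fatigue difference 3. Two-sided alpha .05, power 0.80, 100 per group planned.

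**Assumptions.** (a) Fatigue SD: none is stated. Solving back from 87 per group gives 7.02 (t-test) or 7.06 (normal formula). I use 7.02, so d2 = 3/7.02 = 0.427; using 7.06 moves the joint power by less than 0.01. (b) The correlation rho between the two test statistics is not stated, so a range is shown. (c) 92 analysed per compared group, with 100 as the no-attrition case.

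**Reproducing the plan's figure.** Normal formula: n = 2 × (1.96 + 0.8416)² × 2.4² = 90.4, so 91. The two-sample t-test gives 91.4, so 92. The stated 92 is reproduced. The 87 cannot be checked independently, because its SD is missing.

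**Reading 1: either outcome is enough.** For independent tests the family-wise error is 1 − 0.95² = 0.0975. For correlated tests it is 1 − P(|Z1| < 1.96 and |Z2| < 1.96) under a bivariate normal:

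| rho | 0 | 0.3 | 0.5 | 0.7 | 0.9 |
|---|---|---|---|---|---|
| family-wise error | 0.0975 | 0.095 | 0.091 | 0.083 | 0.070 |

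**Reading 2: both are required.** The expected test statistic is d × √(n/2). At n = 92, √46 = 6.782, giving 0.417 × 6.782 = 2.83 for pain and 0.427 × 6.782 = 2.90 for fatigue. The single-outcome powers are Φ(2.83 − 1.96) = 0.807 and Φ(2.90 − 1.96) = 0.826. At rho 0 the joint power is 0.807 × 0.826 = 0.67. For other values it is the bivariate normal probability that both exceed 1.96:

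| rho | 0 | 0.3 | 0.5 | 0.7 |
|---|---|---|---|---|
| 92 per group | 0.67 | 0.69 | 0.71 | 0.73 |
| 100 per group | 0.72 | 0.74 | 0.75 | 0.77 |

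Allowing for the t-distribution lowers these by up to about 0.01. Joint power reaches 0.80 at 100 per group only at rho about 0.9. For rho from 0.7 down to 0, an 80% joint power needs about 107 to 117 analysed per group.

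**Holm at two-sided 0.05, 92 per group.** The first step tests at 0.025, where t-test power is 0.714 for pain and 0.738 for fatigue. Holm also rejects an outcome at .05 once the other has passed 0.025. At rho 0:
- pain: 0.714 + (0.803 − 0.714) × 0.738 = 0.78
- fatigue: 0.738 + (0.822 − 0.738) × 0.714 = 0.80

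Here 0.803 and 0.822 are the t-test powers at .05. By simulation at rho 0.7 the values are 0.77 and 0.78. The range is therefore about 0.77-0.80 per outcome; 0.71 and 0.74 are only the power guaranteed at the first step.

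**Dependence on the group size.** The Design and Randomization sections randomise patients twice. If allocation is equal (no ratio is stated), Hypothesis 3's contrast of hypnosis plus iACT against mindfulness plus usual care would compare about 200/4 = 50 per cell. Power at .05 would then be about 0.54 for pain and 0.56 for fatigue, before requiring both.

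**The case against.** The strongest reply is that a multiplicity rule and a ranking of analysis populations commonly sit in the SAP, which is not shown, and that sizing each outcome at .05 rules out neither Holm nor a both-must-succeed rule. This stands as far as the missing rule goes. It does not rescue the power statement: the sample size is fixed in the protocol, and a later both-outcomes rule would not make it deliver 0.80.

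Four stronger readings are tempting, and the text does not support them.

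- *Error control is lost outright.* It is not. If both outcomes must be significant, testing each at .05 holds the error for the joint claim at 5%. Hypothesis 3's wording leans that way, although it is not a decision rule.
- *The stated 0.80 is wrong under every reading.* If either outcome is enough, 0.80 is a correct per-outcome power at .05; the fault is then in alpha.
- *Two outcomes, two methods and two populations make eight primary p-values of equal rank.* The 3-month comparison comes first and the mixed models are introduced as additional, which implies an order. Only the two populations are left unranked, and none of the error figures above depends on them.
- *Holm would cut power to 0.71 and 0.74.* Those are plain Bonferroni figures; Holm loses only a few points.

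The per-protocol set is not defined. That it would turn on patients' own use of iACT is plausible from the Compliance section, but not stated.

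**Conclusion.** The concern holds in a conditional form. The protocol sizes two primary outcomes separately and gives no success rule. One of two consequences follows: a family-wise error of about 8-10% (rho 0.7 to 0) if either outcome is enough, or power of about 0.67-0.73 at 92 per group (0.72-0.77 with all 100 analysed) if both are required. The second is the more natural reading of Hypothesis 3, and there the weakness is power, not error control. Which analysis population decides is also open.

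The joint-power and fatigue figures rest on the back-solved fatigue SD of about 7.0. All the ranges rest on an unknown correlation, and all the power figures on 92 or 100 analysed per compared group. The trial remains analysable; what needs correcting is the match between its claim and its stated power.

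**What to change.** In Statistical analyses, make the intention-to-treat comparison at 3 months the decisive analysis for each primary outcome, and label the per-protocol, mixed-model and 6-month results supportive. This keeps the order the protocol already implies.

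In Sample size and power, choose one rule:

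- Apply Holm across pain and fatigue at two-sided 0.05, and state per-outcome power of about 0.77-0.80 at 92 per group, with 0.71 (pain) and 0.74 (fatigue) as the guaranteed first-step power; or
- Declare that both outcomes must be significant at .05, and state power of about 0.67-0.73.

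Either way, state the FACIT-F SD and its source, the assumed range of correlation, and the number analysed in each compared group. Recalculate the power if the Hypothesis 3 contrast uses the smaller cells of the twice-randomised design. The rule should be fixed before any outcome is compared by arm.

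The cost is one paragraph of text and a somewhat lower stated power. No extra data are needed unless the team wants 80% for the both-outcomes claim, which would take more than the planned 100 per group over the correlations from 0 to 0.7.

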## Background

Breast cancer is the most common cancer type among women, with >1 million new cases worldwide every year (1). Survival rates for breast cancer is increasing (2), but for many patients survivorship is also characterized by disabling psychological and physical late effects (3-5). Chronic post-surgical pain (CPSP) and persistent fatigue have the most profound prevalence. CPSP has prevalence rates ranging from 25-60% depending on definition, measurement and treatment (6). In a recent Norwegian study, more than 40% of women treated for breast cancer continued to have pain 2-6 years after surgery (7), while over a third of the women in a large Danish study reported persistent pain 5-7 years after surgery (8).

Persistent fatigue is the most common symptom associated with cancer and its treatments (9). Still, studies on the occurrence of and predictors of fatigue after surgery are scarce. One of the few studies investigating persistent fatigue after surgery reported high levels of fatigue in the first two months after surgery, followed by mild-to-moderate levels of fatigue that persisted 12 months after surgery (10). In another post-operative study, a third of the women struggled with persistent fatigue up to 10 years into survivorship (11)

The pathophysiology of CPSP is still unclear. Presumably, the nature of most CPSP is neuropathic since surgery (e.g. mastectomy) may involve major nerve damage, and is associated with the highest incidence of such pain (12, 13). However, many patients with CPSP do not show any signs of neuropathic pain, or any sensory changes (3). It is thus assumed that the distinct pathophysiology reflects both peripheral and central sensitization as well as humoral factors contributing to pain. Further, the etiology of chronic pain is grounded in the bio-psycho-social model, where psychological and social factors contribute to the

development of CPSP (14). The pathophysiology of post-surgical fatigue is also largely unclear (15). The underlying mechanisms likely vary from patient to patient, with a mixture of biological and psychological underpinnings (16). Interestingly, there are several shared risk factors between pain and fatigue after surgery, including depression and outcome expectancies (17), implying that the very same processes might influence both post-surgical pain and fatigue.

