Unmodifiable risk factors for CPSP involve female gender and younger age (12), as well as preoperative pain conditions and use of opioids (12, 13, 18, 19). However, a preventive intervention could target psychological factors, which are both modifiable, robust and potent predictors of CPSP and fatigue (14, 20). The most frequent tap into anxiety, such as hypervigilance and pain catastrophizing (20-24). Other strong predictors involve depression, stress, and optimism (10, 14, 23).

Despite strong evidence supporting the role of psychological factors in the development of CPSP and fatigue, hardly any studies have investigated psychological and behavioral interventions aimed at preventing these symptoms. CPSP and fatigue *management*, however, has been the aim of several psychological and behavioral interventions. Mindfulness-based cognitive therapy on persistent pain after breast cancer surgery was recently found effective in reducing pain intensity (25), and a study led by a member of our project group found beneficial effects of CBT plus hypnosis to control fatigue in patients undergoing radiotherapy for breast cancer (26). Several studies of similar psychological interventions exist, but with limited effects (27, 28), and with no preventive focus (29-31).

Hypnosis is a non-pharmacotherapeutic technique that holds promise as a harmless and effective pre-operative intervention to alleviate acute post-surgical pain and fatigue (32, 33). Clinical research with at least 20 different surgical populations has indicated that hypnosis can reduce the need for medication, reduce post-surgical symptoms, and enhance recovery (33). Furthermore, meta-analyses (34), narrative reviews (35, 36), and randomized clinical studies (37-40) all support the potential clinical utility of hypnosis with surgical breast cancer patients. A rigorous trial from 2007 demonstrated particularly large effects of a specific 15-minute pre-operative hypnosis on analgesic needs, pain intensity and fatigue after breast cancer surgery (41). However, the results from this trial have not been replicated, and results from hypnosis trials in general lack long-term follow-up.

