### ***Inclusion criteria***

Patients must fulfill the following criteria to be eligible for inclusion in the study:

- Women diagnosed with breast cancer and scheduled for surgery
- Be able to provide informed consent
- Over the age of 18

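### The control NRS of 5 (SD 2.4) is taken from a trial in women with persistent pain, but this trial enrols all surgical patients, so the planning values and the 80% power need restating for an unselected cohort

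*Protocol*

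**What the plan says.** The protocol's section on sample size and power fixes the inputs for the primary pain outcome. The difference is given as "We thus expect a minimum difference of one point on NRS (0-10) and 3 points on FACIT-F". For the control arm, "it is expected that the control group scores 5 (SD: 2.4) on NRS at 3 months follow-up (25), and 18 on FACIT-F (26"). The test is two-sided at 5% with 80% power, the requirement is 92 per group for pain, and 100 per group are planned to allow for attrition.

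The source of the mean and SD is reference 25. The Background describes it thus: "Mindfulness-based cognitive therapy on persistent pain after breast cancer surgery was recently found effective in reducing pain intensity (25"). That sentence stands in a paragraph contrasting symptom management with prevention. The title in the reference list refers to late post-treatment pain.

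The inclusion criterion that defines the population is "Women diagnosed with breast cancer and scheduled for surgery"; the others concern consent and age. Neither the inclusion nor the exclusion criteria mention pain. The statistical analysis section compares pain levels at 3 months without restricting to women who have pain. On how many women have lasting pain, the Background says "CPSP has prevalence rates ranging from 25-60% depending on definition, measurement and treatment".

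**The concern.** A treatment trial in persistent pain starts with women who hurt. A prevention trial that randomises before surgery ends with some women in pain and others with little or none. Its arm mean should be lower, and its NRS distribution is likely to be a mixture with many scores near zero. The protocol gives the whole control arm the mean and SD of the first kind of trial.

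Two things follow. The SD enters the sample size directly, and mixing women with and without pain usually raises it. The mean does not enter the formula, but it determines how large one point is relative to the pain available to be prevented. If the pain result is null, readers will judge it against a stated 80% whose inputs do not describe the enrolled population.

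**Working it through.** **Inputs.** From the sample size section: difference 1 point, SD 2.4, control mean 5, two-sided alpha 0.05, power 0.80, 92 per group needed, 100 planned. From the Background: chronic pain in 25-60%. My assumptions: women with pain at 3 months score as in reference 25 (mean 5, SD 2.4); the others score 0 or, alternatively, average 1 (SD 1).

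**Step 1: the plan's own figure.** n = 2(1.960 + 0.842)² × 2.4² / 1² = 90.4, so 91 per group by the normal approximation. The t-test gives 91.4, so 92. The stated figure is reproduced. Power by t-test is 0.80 at 92 and 0.83 at 100 per group.

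**Step 2: does a mean of 5 fit 25-60%?** If a share p has pain and the others average m0, women with pain must average (5 − (1 − p)m0)/p.

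- Others at 0: 5/0.60 = 8.3; 5/0.40 = 12.5; 5/0.25 = 20.
- Others at 1: (5 − 0.4)/0.60 = 7.7; (5 − 0.6)/0.40 = 11; (5 − 0.75)/0.25 = 17.

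The 40% and 25% cases are impossible on a 0-10 scale. If women with pain average 5 and the others less, an arm mean of 5 requires everyone to have pain.

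**Step 3: mean and SD of the mixture.**

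Mean = 5p + (1 − p)m0. Variance = p × 2.4² + (1 − p)s0² + p(1 − p)(5 − m0)².

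Example, p = 0.40 with others at 0: mean 2.0; variance 0.40 × 5.76 + 0.24 × 25 = 8.304; SD 2.88.

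**Step 4: power for one point.** Two-sample t-test, 92 per group, mixture SD in both arms. At 92 per group the difference detectable with 80% power is about 0.415 × SD.

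| Others | p | Control mean | SD | 1 point as % of mean | Power, 1 point | Detectable difference |
|---|---|---|---|---|---|---|
| 0 | 25% | 1.25 | 2.48 | 80% | 78% | 1.03 |
| 0 | 40% | 2.0 | 2.88 | 50% | 65% | 1.20 |
| 0 | 60% | 3.0 | 3.08 | 33% | 59% | 1.28 |
| 1 (SD 1) | 25% | 2.0 | 2.28 | 50% | 84% | 0.95 |
| 1 (SD 1) | 40% | 2.6 | 2.60 | 38% | 74% | 1.08 |
| 1 (SD 1) | 60% | 3.4 | 2.77 | 29% | 68% | 1.15 |

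Under the planned mean of 5, one point is 1/5 = 20%. The SD exceeds 2.4 in five of the six rows. With all 100 per group evaluable, power is 81/69/63% (others at 0) and 87/77/72% (others at 1).

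**Step 5: a benefit confined to women with pain (my assumption, not the protocol's).** If those women improve by one point and the others do not change, the arm difference is p × 1 = 0.25, 0.40 or 0.60. With the SDs above and 92 per group, power is 0.105, 0.155 and 0.260 (others at 0) or 0.115, 0.180 and 0.309 (others at 1), about 10-31%.

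**Step 6: higher prevalence at 3 months.** At an assumed p = 80%, the control mean is 4.0 (others at 0) or 4.2 (others at 1), the SD 2.93 or 2.71, and power for one point 63% or 70%.

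**The case against.** The strongest reply is that the control mean is not in the two-means formula. This is true, and 92 per group is not an arithmetic error. A reader might infer that the prevalence range alone contradicts the 80% power. It does not: power depends on the difference and the SD, and at 25% prevalence it stays at 78-84%.

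The 25-60% range is for chronic pain and varies with definition, and the two cohort figures beside it come from years after surgery. The endpoint is at 3 months, when some women may be having further treatment. The documents give no 3-month prevalence or mean, and it could be higher. This limit stands. It is why the arm mean is called likely lower and why the 80% case is shown.

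The entry threshold of reference 25 is not in the protocol. Its population is known here from one sentence and a title, which is enough to question the input but not to measure the error.

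A reader might also object that the section says "we expect more heterogeneity in our data as our study population will undergo several medical treatments" and yet leaves the SD at 2.4. The documents do not support that charge. The comparison is with the trials in references 26 and 60, not with reference 25, and the section uses the point to justify a smaller difference. It does not address women with little or no pain.

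Finally, the FACIT-F SD is not stated. That is a reporting gap: 87 per group for 3 points implies an SD of about 7.0. It does not show the fatigue calculation to be wrong.

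**Conclusion.** The point holds as a fault in the planning inputs. The NRS mean and SD come from a population with persistent pain, the trial enrols women without regard to pain, and a whole-arm mean of 5 does not fit the protocol's own prevalence range.

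If 25-60% of women have pain scored as in reference 25, power for one point at 92 per group is about 59-84%, and one point is 29-80% of control pain rather than 20%. These figures rest on the assumed scores of the other women, a common SD in both arms, and a prevalence range not specific to 3 months.

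It would be tempting to conclude that the trial has only 10-31% power. That figure requires the benefit to be confined to women with pain. The protocol states an absolute one-point difference between arms and plans no relative or subgroup effect, so the figure shows sensitivity to an assumption and is not the trial's power.

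**What to change.** In the sample size section, replace the NRS mean and SD with values for unselected patients about 3 months after breast cancer surgery. If no such source is available, give a range of assumptions: the share with pain, and the mean and SD in women with and without it. Prevalence alone does not yield a mean or an SD.

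Over that range, restate the power for one point and the difference detectable with 80% power at the fixed 200 patients, and say what proportion of expected control pain one point represents.

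The cost is one rewritten paragraph and, in most scenarios, a less favourable stated power. Enrolment does not change.
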